## Abstract

Background: Cardiogenic shock and arrest present as critical, life-threatening emergencies characterized by severely compromised tissue perfusion and inadequate oxygen supply. Veno–arterial extracorporeal membrane oxygenation (VA–ECMO) serves as a mechanical support system for patients suffering shock refractory to conventional resuscitation. Despite the utilization of VA–ECMO, clinical deterioration due to systemic inflammatory response syndrome (SIRS) resulting from the underlying shock and exposure of blood cells to the artificial surfaces of the ECMO circuit may occur. To address this issue, cytokine adsorbers offer a valuable solution by eliminating blood proteins, thereby controlling SIRS and potentially improving hemodynamics. Consequently, a prospective, randomized, blinded clinical trial will be carried out with ECMOsorb. Methods and Study Design: ECMOsorb is a single-center, controlled, randomized, triple-blinded trial that will compare the hemodynamic effects of treatment with a VA–ECMO in combination with a cytokine adsorber (CytoSorb^®^, intervention) to treatment with VA–ECMO only (control) in patients with cardiogenic shock (with or without prior cardiopulmonary resuscitation (CPR)) requiring extracorporeal, hemodynamic support. Fifty-four patients will be randomized in a 1:1 fashion to the intervention or control group over a 36-month period. The primary endpoint of ECMOsorb is the improvement of the Inotropic Score (IS) 72 h after the intervention. Prognostic indicators, including mortality rates, hemodynamic parameters, laboratory findings, echocardiographic assessments, quality of life measurements, and clinical parameters, will serve as secondary outcome measures. The safety evaluation encompasses endpoints such as air embolisms, allergic reactions, peripheral ischemic complications, vascular complications, bleeding incidents, and stroke occurrences. Conclusions: The ECMOsorb trial seeks to assess the efficacy of a cytokine adsorber (CytoSorb^®^; CytoSorbents Europe GmbH, Berlin, Germany) in reducing SIRS and improving hemodynamics in patients with cardiogenic shock who are receiving VA–ECMO. We hypothesize that a reduction in cytokine levels can lead to faster weaning from inotropic and mechanical circulatory support, and ultimately to improved recovery.

## 1. Introduction

In Europe, the yearly occurrence of cardiogenic shock resulting from cardiac arrest is estimated to range between 67 and 170 cases per 100,000 inhabitants [1]. When considering shock attributed to heart failure as well, the number rises to approximately 500,000 individuals [2]. However, poor overall survival persists, especially after cardiac arrest with a survival rate upon hospital discharge ranging from 0% to 18%, with an overall average of 8% [1].

The integration of percutaneous, mechanical, extracorporeal support for oxygenation and circulation serves as a secondary line of treatment for achieving hemodynamic stabilization [3,4] and veno-arterial extracorporeal membrane oxygenation (VA–ECMO) serves as a rescue therapy for patients experiencing shock that is unresponsive to conventional resuscitation efforts [3,5,6,7]. It functions as a bridging intervention, ensuring the maintenance of organ perfusion while the underlying cause of the shock is identified and addressed [3]. This treatment approach has demonstrated encouraging survival rates falling within the range of 20% to 30% [3,8,9].

Conditions that may necessitate ECMO support, such as cardiogenic shock or cardiac arrest, exhibit a shared pathogenetic mechanism of clinical deterioration, characterized by hyperinflammation [10,11,12]. This systemic inflammatory response syndrome (SIRS), which occurs to varying degrees in the majority of patients on ECMO support, is typically not infection-driven but rather a response to tissue injury associated with the underlying condition [12]. Furthermore, the ECMO support itself can trigger and sustain an inflammatory response through diverse mechanisms, including the contact between blood cells and molecules with the artificial surfaces of tubing, rotor, and oxygenator within the ECMO circuit [12,13]. Due to SIRS, the consequent development of multiorgan dysfunction syndrome (MODS) leads to a significant reliance on inotropic support. The administration of high doses and/or multiple different inotropes not only fails to alleviate tissue hypoxia and systemic inflammation but often exacerbates them, ultimately leading to increased mortality rates [12,14,15,16,17].

Extracorporeal hemoadsorption has emerged as a promising and innovative therapeutic approach to address this circumstance. Technological advancements have reached a stage where the properties of novel polymers can be harnessed for blood purification therapy. These polymers facilitate the selective and concentration-dependent removal of cytokines and other inflammatory mediators, offering a potential solution for targeted filtration [18,19]. CytoSorb^®^ (CytoSorbents Europe GmbH, Berlin, Germany) is a commercially available cytokine adsober which uses that concept [20]. Excessive levels of inflammatory mediators, including cytokines, interleukins, anaphylatoxins, as well as damage- and pathogen-associated molecular patterns, are irreversibly bound within the polymer through physico-chemical interactions [12].

In summary, the clinical necessity for interventions aimed at addressing inflammation and its cytokine storm is evident. Various strategies employed to manage the systemic inflammatory response through direct or indirect methods, such as steroids [12,21], plasma exchange [12,22], toll-like receptor antagonists [12,23], nitric oxide synthase inhibitors [12,24], or scavenger hemoglobin derivatives [12,25], have yielded conflicting or inconclusive outcomes, limiting their widespread application [12,26].

The ECMOsorb trial is designed to investigate the changes in hemodynamics, inflammatory biomarkers and immune system after implantation of a VA–ECMO in combination with an extracorporeal cytokine hemadsorption system.

## 2. Methods and Analysis

### 2.1. Study Design

ECMOsorb is an interventional, prospective, two-arm randomized, controlled, triple-blinded trial. ECMOsorb will determine if the early, additional use of CytoSorb^®^ (CytoSorbents Europe GmbH, Berlin, Germany) is superior to standard ICU–treatment alone in patients with cardiogenic shock under VA–ECMO support. Figure 1 shows the flowchart of the trial. For patients in the interventional study arm, the CytoSorb^®^ hemadsorption device will be integrated into the VA–ECMO circuit within 6 h after ECMO implantation by a cardiac technician (perfusionist). The intervention phase is set for 72 h. The device will be changed every 24 h.

Each patient will be limited to a maximum of three adsorbers. Within the control group, patients will undergo VA–ECMO with the integration of a standard tube into the ECMO circuit, in place of the hemadsorption device. This integration task will be carried out by a proficient perfusionist.

Regardless of group allocation, the hemadsorption device as well as the normal tube will be encapsulated by an always identically looking “black box” to ensure blinding (Figure 2 and Figure 3). Both groups will receive the VA–ECMO and standard of care for cardiogenic shock. Except for the adsorber, all other procedures and collected data will be identical in the two groups. An administration of the adsorber outside of this study for these patients will not take place. Only the perfusionist will be aware of treatment allocation. The interventionalist, the treating ICU team and the rest of the study team will thus be unaware of the group allocation. No interim analysis is planned or will be performed.

### 2.2. Study Population

Critically ill patients with cardiogenic shock with or without cardiopulmonary reanimation (CPR) and indication for VA–ECMO will be included.

### 2.3. Time Schedule, Study Duration and Frequency of Study Visits

The study is projected to span a period of 43 months, comprising a 36–month recruitment phase, a 1-month final follow-up period, and an additional 6 months dedicated to data analysis. The duration of intervention per patient is 72 h or termination of VA–ECMO (whichever occurs first). Follow-up per patient is 30 days after the beginning of the intervention. Table 1 outlines the study visits.

### 2.4. Screening and Randomization

All patients with cardiac shock requiring hemodynamic support via VA–ECMO referred to our department will be screened. Patients will be 1:1 randomized into one of the two groups.

### 2.5. Obtaining Informed Consent

Before inclusion, the nature, the aim and full extent of study participation will be explained to each subject, their legally authorized representative or an independent medical doctor, according to the Declaration of Helsinki to obtain informed consent.

### 2.6. Objectives

#### 2.6.1. Primary Objective

The primary objective of this study will be to demonstrate the benefit of a cytokine hemoadsorption device (CytoSorb^®^) compared to no device on hemodynamics of patients with cardiogenic shock under VA–ECMO treatment.

#### 2.6.2. Secondary Objective

The main focus of the secondary objectives will be to gain knowledge and study the mechanisms of subsequent prevention/limitation of the development of a cytokine-derived SIRS/multiple organ dysfunction syndrome (MODS) in these selected patients. Apart from laboratory parameters, the secondary objectives mostly include clinical surrogate measures (e.g., mortality) to confirm potential advantages of CytoSorb^®^ during the intervention and follow-up phase. Data acquisition during hospitalization and follow up is displayed in Table 1.

### 2.7. Endpoints

#### 2.7.1. Primary Endpoint

The primary endpoint of the ECMOsorb trial is the mean difference of the Inotropic Score (IS) 72 h after randomization (implantation of CytoSorb^®^ or a normal ECMO tube) between the two study arms. The Inotropic Score is calculated as: dopamine dose [μg/kg/min] + dobutamine dose [μg/kg/min] + 100xepinephrine dose [μg/kg/min] + 100× norepinephrine [μg/kg/min].

The role of dopamine in the management of cardiogenic shock remains a topic of debate. It has been observed that the administration of dopamine is associated with an increased incidence of arrhythmic events and higher mortality rates among patients with cardiogenic shock [27,28]. As a result, dopamine is not included in the repertoire of inotropic agents and vasopressors employed for the treatment of acute heart failure at our study site.

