#### 2.7.2. Secondary Endpoints of the Study Are as Follows (Selection)

Duration of renal replacement therapy (continuous venovenous hemodialysis (CVVHD)), mechanical ventilation, ECMO therapy, inotropic/vasopressor treatment 7 and 30 days after the beginning of the intervention.

30–day mortality defined as mortality, in the hospital or anywhere after discharge, within 30 days after the beginning of the intervention.

Changes in mediators/markers of inflammation, myocardial damage, oxidative stress, myocardial wall stress, myocardial remodeling, kidney injury and kidney function at baseline, every 24 h during the intervention phase (up to 72 h) and on day 7 after the beginning of the intervention.

Length of stay in ICU and total length of hospital stay until discharge/transfer within 30 days after the beginning of the intervention.

Echocardiographic parameters of left and right ventricular function at baseline, every 24 h during the intervention phase (up to 72 h) and on day 7 after the beginning of the intervention.

Marker of hemolysis every 24 h under ECMO treatment (up to 72 h) after the beginning of the intervention.

Implantation of an active assist device or heart transplantation assessed on day 30 after the beginning of the intervention.

Simplified acute physiology score (SAPS) II, acute physiology and chronic health evaluation (APACHE) II; sequential organ failure assessment (SOFA) score at baseline, every 24 h during the intervention phase (up to 72 h) and on day 7 after the beginning of the intervention.

EQ–5D–3L questionnaire including EQ VAS (visual analogue scale), rehospitalization due to heart failure measured 30 days after the beginning of the intervention.

Neurological outcome: mRS (modified Rankin Scale), incidence of apoplexy, Glasgow Coma Scale (GCS), neuron-specific enolase (NSE), S–100, cerebral performance category (CPC), if clinically necessary and available: Computed tomography (head CT)/medianus somatosensory evoked potential (SEP) at baseline, every 24 h during the intervention phase (up to 72 h), on day 7 and on day 30 after the beginning of the intervention.

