**General examination**							
Medical history, comorbidities ^∆^	X		X				
Physical examination ^∆^	X		X	X			
Prior/concomitant medication ^∆^	X		X	X			
Neurological exam (incl. mRS) ^∆^	X		X	X	X	X	X
Quality of Life (EQ -5D-3L including EQ VAS)						X	X
SCOREs (SAPS II, APACHE II, SOFA) ^∆^	X			X	X	X	
Adverse events/complications ^∆^				X *	X	X	X

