**Diagnostic procedures**							
12-lead surface ECG ^∆^	X		X	X	X		
TTE ^∆^	X		X	X	X	X	
Technical data from ECMO ^∆^	X			X	X	X	
Laboratory evaluation ^∆^	X		X	X	X	X	
Local blood chemistry ^∆^	X		X	X	X		
PAC–Hemodynamics ^∆^	X			X	X		
Measurement of parameters of hemodynamics ^∆^	X		X	X	X	X	
Measurement of mortality ^∆^	X					X	X
Measurement of duration of ECMO, ventilation, dialysis, inotropic therapy ^∆^	X			X	X	X	X
Measurement of the neurological outcome ^∆^	X			X	X	X	X
VA–ECMO Implantation	X			X			

^∆^ Data documentation from clinical routine (if available). * Recording of AEs/SAEs after implantation of CytoSorb® adsorber or ECMO tube, ^†^ device = either CytoSorb^®^ adsorber (= intervention group) or ECMO tube (= control group) via black box. ^1^ within the first 6 h after implantation of VA-ECMO, ^2^ changed every 24 h within the intervention of 72 h, V = visit, mRS = modified Rankin Scale, SAPS = Simplified Acute Physiology Score, APACHE = Acute Physiology And Chronic Health Evaluation, SOFA = sepsis-related/sequential organ failure assessment score, ECG = electrocardiography, TTE = transthoracic echocardiogram, ECMO = Extracorporeal membrane oxygenation, PAC = pulmonary artery catheterization, VAS = visual analogue scale, h = hours.

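### The primary Inotropic Score gives no points to vasoactive drugs outside four named agents, and the visit table shows no record of agent and dose at 72 h, so a partial drug switch can count as improvement

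*Protocol article*

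**What the plan says.** Section 2.7.1 of the Protocol article defines the primary endpoint as "the mean difference of the Inotropic Score (IS) 72 h after randomization" between the two arms. The score is the sum "dopamine dose [μg/kg/min] + dobutamine dose [μg/kg/min] + 100xepinephrine dose [μg/kg/min] + 100× norepinephrine [μg/kg/min". The same section states that "dopamine is not included in the repertoire of inotropic agents and vasopressors employed for the treatment of acute heart failure at our study site". No other drug has a term.

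Other parts of the article speak of vasoactive support more broadly. The inclusion criteria (section 2.8) refer to inotropic agents and/or vasopressors without listing them. The secondary endpoints (section 2.7.2) include the duration of "inotropic/vasopressor treatment 7 and 30 days after the beginning of the intervention", also without a list.

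Three rows of Table 1 matter here:

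- "Prior/concomitant medication" is marked under routine examination, screening and V0. It is blank at V1, V2 and V3.
- "Measurement of duration of ECMO, ventilation, dialysis, inotropic therapy" is marked at V0, V1, V2 and V3.
- "Measurement of parameters of hemodynamics" is marked at screening, V0, V1 and V2, and its content is not itemised.

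The primary model (section 2.12.2) contains treatment and baseline score only. The treating ICU team is blinded (section 2.1).

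**The concern.** The trial hypothesis concerns weaning from inotropic support as a whole, but the primary endpoint sees only the named catecholamines. If an unscored agent takes over part of the norepinephrine or epinephrine dose, the score loses 100 points for each μg/kg/min spared and gains nothing for the replacement. The patient then looks better on the primary endpoint without needing less support.

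Such use would follow the patient's condition, and condition is what the device is meant to change. If add-on agents go to patients who are doing badly and the adsorber works, controls would receive more of them. Their scores would be understated and the measured benefit would shrink. If the adsorber harms, the primary endpoint would understate the harm. A model with only treatment and baseline score cannot correct for drug changes after randomisation.

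**Working it through.** **1. The plan's own figure.** Inputs from section 2.12.1: SD 5.6, difference 5 points, power 80%, two-sided α = 0.05, independent-samples t test. The noncentral t calculation gives 20.70, so 21 per group, with power 80.6%. Dropout: 21 / (1 − 0.20) = 26.25, so 27 per group and 54 in total. Both figures reproduce. The stated total of 44 is not 2 × 21 = 42; that is a separate slip and plays no part below.

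**2. What the target means in drug dose.** The weight of norepinephrine and epinephrine is 100 (section 2.7.1), so:

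- target difference: 5 / 100 = 0.05 μg/kg/min
- SD: 5.6 / 100 = 0.056 μg/kg/min

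This translates one patient's score. It is not the shift in an arm mean: one patient of 21 whose score falls by 5 points moves the mean by 5 / 21 = 0.24 points.

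**3. Use that differs between arms (assumed).** Bias in the mean difference = difference in the share of patients using an unscored agent × points spared per user. Sparing 0.05 to 0.10 μg/kg/min is 5 to 10 points. The last column takes a true difference of 5 in favour of the adsorber, more unscored use among controls, SD held at 5.6 and 21 per group.

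| Difference in use | Points spared | Bias | Share of target | Power for 5 − bias |
|---|---|---|---|---|
| 10% | 5 | 0.5 | 10% | 72% |
| 10% | 10 | 1.0 | 20% | 62% |
| 20% | 5 | 1.0 | 20% | 62% |
| 20% | 10 | 2.0 | 40% | 40% |
| 30% | 5 | 1.5 | 30% | 51% |
| 30% | 10 | 3.0 | 60% | 20% |

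**4. Equal use in both arms (assumed).** With share q and x points spared, independent of the underlying score, SD = √(5.6² + q(1 − q)x²).

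- Mildest case, q = 0.10 and x = 5: √(31.36 + 2.25) = 5.80; power with 21 per group 78%; 23 per group for 80% power.
- Strongest case, q = 0.30 and x = 10: √(31.36 + 21.00) = 7.24; power 59%; 34 per group for 80% power.

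One caution: the SD of 5.6 comes from the site's own VA-ECMO patients. If unscored agents were used there at a similar rate, this noise is already in the 5.6 and step 4 counts it twice. Step 3 does not depend on that.

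**5. What Table 1 would reveal.** The score cannot be calculated without doses of the scored drugs at 72 h, yet no row names them. Some drug data must therefore be captured during V1 outside the medication row. What the table does not show is whether that capture extends to agents outside the formula. The duration row could show that support continued, but not with which drug or at what dose.

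**The case against.** The strongest reply is that the premise is not in the article: nothing says that any unscored inotrope or vasopressor is used at this site. That stands. Substitution is a possibility, and the shares and the sparing above are assumptions.

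A reader might infer from the blank medication row that substitution would go entirely unseen. The document does not support this. Duration of inotropic therapy is recorded at every visit from V0 to V3, inotropic/vasopressor duration is a secondary endpoint, and the full CRF may already itemise infusions. An article need not reproduce the CRF.

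A reader might also infer that one switched patient wipes out the target difference. That sets an individual score against a difference in means; the shift is about 0.24 points in an arm of 21. Nor must a sicker patient score better: an agent added on top of high catecholamine doses can still leave a high score. The unused dopamine term is harmless, since it adds zero in both arms.

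Blinding rules out differences that come from knowing the allocation. It does not rule out differences that come from patient condition. Attenuation of a true benefit is conservative for a superiority claim, but it costs power. Masked harm could still appear in mortality, SOFA and the support durations.

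Finally, a dose score and a duration endpoint are meant to measure different things, so their differing scope is not a contradiction. What remains is that the formula is closed and the article gives no way to test whether the result depends on that.

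**Conclusion.** The concern holds in a limited form. The primary score has no term for vasoactive drugs outside its formula, so under the plan as written a partial switch to such a drug can count as improvement. The planned model does not adjust for this, and the visit table shows no record of agent and dose at 72 h that would let it be checked.

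The size is unknown. A bias of 0.5 to 3.0 points, or 10% to 60% of the 5-point target, requires use at 72 h to differ between arms by 10 to 30 percentage points with 0.05 to 0.10 μg/kg/min of norepinephrine spared per user. With equal use the main effect is noise, with power between 59% and 78% under the same assumed ranges, unless the planning SD already contains it. If unscored agents are hardly used at the site, the effect is negligible. The stated score is usable as the primary endpoint; it needs a check beside it.

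**What to change.** 1. Extend the concomitant-medication row of Table 1 to V1 so that every vasoactive infusion and its dose at 72 h is captured, or confirm that the CRF already does this.
2. Keep the stated Inotropic Score as the primary endpoint.
3. Pre-specify one sensitivity analysis with an extended score that includes the unscored inotropes and vasopressors, using the same linear model, with the weights fixed before unblinding.
4. Report by arm the number of patients on an unscored agent at 72 h. If the two scores disagree, qualify any conclusion about reduced inotropic need.

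The cost is a little extra data entry from the ICU chart for 54 patients and one more analysis. No treatment changes.

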#### 2.7.2. Secondary Endpoints of the Study Are as Follows (Selection)

Duration of renal replacement therapy (continuous venovenous hemodialysis (CVVHD)), mechanical ventilation, ECMO therapy, inotropic/vasopressor treatment 7 and 30 days after the beginning of the intervention.

30–day mortality defined as mortality, in the hospital or anywhere after discharge, within 30 days after the beginning of the intervention.

Changes in mediators/markers of inflammation, myocardial damage, oxidative stress, myocardial wall stress, myocardial remodeling, kidney injury and kidney function at baseline, every 24 h during the intervention phase (up to 72 h) and on day 7 after the beginning of the intervention.

Length of stay in ICU and total length of hospital stay until discharge/transfer within 30 days after the beginning of the intervention.

Echocardiographic parameters of left and right ventricular function at baseline, every 24 h during the intervention phase (up to 72 h) and on day 7 after the beginning of the intervention.

Marker of hemolysis every 24 h under ECMO treatment (up to 72 h) after the beginning of the intervention.

Implantation of an active assist device or heart transplantation assessed on day 30 after the beginning of the intervention.

Simplified acute physiology score (SAPS) II, acute physiology and chronic health evaluation (APACHE) II; sequential organ failure assessment (SOFA) score at baseline, every 24 h during the intervention phase (up to 72 h) and on day 7 after the beginning of the intervention.

EQ–5D–3L questionnaire including EQ VAS (visual analogue scale), rehospitalization due to heart failure measured 30 days after the beginning of the intervention.

Neurological outcome: mRS (modified Rankin Scale), incidence of apoplexy, Glasgow Coma Scale (GCS), neuron-specific enolase (NSE), S–100, cerebral performance category (CPC), if clinically necessary and available: Computed tomography (head CT)/medianus somatosensory evoked potential (SEP) at baseline, every 24 h during the intervention phase (up to 72 h), on day 7 and on day 30 after the beginning of the intervention.

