#### 2.10.2. VA–ECMO Weaning

Initiating weaning from VA–ECMO involves an individualized strategy that requires hemodynamic stability, an improvement of left ventricular pump function and a controlled underlying cause of cardiogenic shock. Patients experiencing ongoing cardiac failure are deemed unable for weaning. A daily evaluation to assess the potential for weaning is implemented using clinical, laboratory, and echocardiographic data that either favor weaning or may be suggestive for difficulties in weaning. Criteria for initiating a weaning attempt include (selection): a left ventricular ejection fraction (EF) of at least 20%, pulsatile flow, normalized arterial lactate, a mean arterial pressure of at least 65–70 mmHg, low requirement of vasopressor or inotropic support, oxygen saturation nearly 95%, central venous oxygen concentration >60% and a low ventilatory support for normal lung ventilation and oxygenation while on VA–ECMO support. Weaning is initiated by gradually reducing VA–ECMO pump flow while monitoring cardiac function continuously. If signs of inadequate cardiac output or tissue perfusion, e.g., increasing blood lactate levels, are observed, the patient will be returned to higher VA–ECMO support. Once a minimal VA–ECMO support (<2 L per minute) has been established during the weaning process, ensuring hemodynamic stability, termination of the extracorporeal circulation will take place and the cannulas will be clamped. Immediate decannulation using access site closure devices such as Angioseal^®^ (TERUMO^®^, Somerset, NJ, USA) and/or ProGlide^®^ (Abbott Park, IL, USA) will be performed at the bedside for percutaneously placed cannulas. Central cannulation or surgical cutdown requires cannula removal in the operating room. After complete and successful weaning, continuous monitoring of cardiac output is necessary to ensure organ perfusion is maintained. Additional ongoing inotropic support may be required for certain patients. Patients unsuitable or unable for weaning will be considered for transplant or assist device implantation (LVAD).

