#### 2.12.2. Statistics

The primary outcome analysis will involve comparing the experimental group receiving CytoSorb^®^ with the control group receiving standard care (without CytoSorb^®^), focusing on the differences in the mean Inotropic Score (IS) at 72 h post-implantation. The primary analysis will encompass the full analysis set, including all patients who were randomized and received treatment, following the intent-to-treat (ITT) principle. Sensitivity analyses are planned in the per-protocol (PP) analysis set. A linear model will be fitted for the primary endpoint with treatment and baseline IS as fixed effects. The confirmatory analysis will be performed at a significance level of 5%. The mean difference of the primary endpoint will be estimated within the model and will be reported with 95% confidence interval. Categorical endpoints will be compared by Chi-square test/Fisher’s exact test between groups. According to the data distribution, two-sided independent samples *t* test or Mann–Whitney U test will be applied for continuous endpoints. Adequate descriptive statistics will be used to summarize the data in each group. All secondary analyses will be performed exploratively, i.e., without adjustment for multiplicity. Safety analyses will be run in the safety population to be defined in the protocol; these analyses will summarize and tabulate all observed safety events including a measure of uncertainty (i.e., 95% confidence intervals).

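### Comparing raw ECMO duration does not separate successful weaning from LVAD/transplant or death, so it is a poor test of the faster-weaning hypothesis

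*Protocol article*

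**What the plan says.** Section 2.7.2 of the protocol article lists the durations of several therapies as one secondary endpoint, among them "mechanical ventilation, ECMO therapy, inotropic/vasopressor treatment 7 and 30 days after the beginning of the intervention". It does not name the event that ends the ECMO count. The same section has 30-day mortality and, as a further endpoint, "Implantation of an active assist device or heart transplantation assessed on day 30 after the beginning of the intervention".

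For the analysis, section 2.12.2 says that, depending on the distribution, a "two-sided independent samples *t* test or Mann–Whitney U test will be applied for continuous endpoints". It names no method for competing events and makes all secondary analyses exploratory, without multiplicity adjustment.

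Section 2.10.2 describes two ways off ECMO for a living patient. When minimal flow is tolerated, "termination of the extracorporeal circulation will take place and the cannulas will be clamped". Otherwise, "Patients unsuitable or unable for weaning will be considered for transplant or assist device implantation (LVAD").

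The Abstract states the hypothesis that "a reduction in cytokine levels can lead to faster weaning from inotropic and mechanical circulatory support". The Discussion puts ICU mortality among the site's ECMO patients at about 80%.

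**The concern.** Of the listed endpoints, ECMO duration comes closest to the weaning part of the hypothesis, and under that hypothesis a shorter duration would be read as benefit. A t test or Mann–Whitney U test uses only the number of days and not the reason why ECMO ended. Weaning fulfils the hypothesis. LVAD or transplant because weaning was not possible does not, and neither does death on ECMO. All three stop the clock.

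At stake is the reading of this secondary result. A difference between arms could reflect more weaning, more or earlier bridging, or earlier death. A real difference in weaning could also be diluted or hidden.

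**Working it through.** The article gives no figure for ECMO duration, bridging rate or bridging time, so there is no stated result to reproduce. Its one calculated figure, the sample size, belongs to the primary endpoint and does not enter here. The days and shares below are assumptions used to show the mechanism.

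**1. One patient.** For a patient bridged on day b, the raw count is b. Time without successful weaning, read to day 30, is 30, because the patient is never weaned. The raw count is therefore too short by 30 − b: 26 days for b = 4, 24 for b = 6 and 16 for b = 14. The same holds for a patient who dies on ECMO on day b.

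**2. One arm against the other.** Assume that weaned patients come off on day 8, and that an extra share s of one arm is bridged on day b instead of being weaned.

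- Change in mean raw duration = s × (b − 8).
- Change in mean days without successful weaning = s × (30 − 8) = s × 22.

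| Bridging day b | Raw duration, s = 5% / 10% / 20% | Days without weaning, s = 5% / 10% / 20% |
|---|---|---|
| 4 | −0.2 / −0.4 / −0.8 | +1.1 / +2.2 / +4.4 |
| 8 | 0 / 0 / 0 | +1.1 / +2.2 / +4.4 |
| 14 | +0.3 / +0.6 / +1.2 | +1.1 / +2.2 / +4.4 |

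With 27 patients per arm, these shares are 1.4, 2.7 and 5.4 patients. The arm with more failed weaning looks better on raw days in the first row, equal in the second, and only slightly worse in the third. These are the wrong-signed, blind and diluted cases.

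**3. Dependence of the sign on timing.** Take a different weaning distribution: 2 days plus an exponential with mean 9 days, capped at day 30. Its mean is 2 + 9 × (1 − e^(−28/9)) ≈ 10.6 days. If 30% are bridged on day 7, mean raw duration falls to 0.7 × 10.6 + 0.3 × 7 ≈ 9.5. With bridged patients set to 30, the mean rises to 0.7 × 10.6 + 0.3 × 30 ≈ 16.4. If bridging is moved to day 14, mean raw duration rises to 0.7 × 10.6 + 0.3 × 14 ≈ 11.6. The sign changes where the bridging day equals the mean weaning time.

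**4. Death.** If the trial matched the site's figure, 54 × 0.8 ≈ 43 patients would die in ICU and about 11 would survive, or 27 × 0.2 ≈ 5 per arm. The formulas in step 2 apply with the day of death in place of b. Not every ICU death occurs on ECMO, but death is probably the commoner way of leaving ECMO unweaned.

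**The case against.** The strongest answer is that the article states no rule for ending the count. It is a condensed document, its endpoint list is marked as a selection, and the full protocol or SAP may define the end event. The sentence on tests is also generic. This limits confidence. It does not remove the point, because the article does name the tests for continuous endpoints, and neither test on raw durations can separate the reasons for stopping.

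A reader might infer that failed weaning will count as a short, favourable duration, so that the endpoint points the wrong way. The documents do not support that. It needs bridging to come earlier than weaning would have, and section 2.10.2 gives no timing. It describes daily assessment, a return to higher support when a weaning attempt fails, and only consideration for LVAD or transplant. Bridging may well come late, and then raw duration moves in the right direction, though by less than it should.

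The shifts are also small. With an SD of roughly 8 days, as in the distribution of step 3, the standard error of a difference between arms of 27 is 8 × √(2/27) ≈ 2.2 days, against shifts in raw duration of at most 1.2 days. Reversal of a result by bridging alone is unlikely.

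Bridging and 30-day mortality are reported as endpoints of their own, so a reader can set them beside duration. That helps interpretation but does not change what the duration test compares. Finally, days on ECMO is a legitimate measure of exposure to the therapy, and nothing in the article labels it the formal test of the weaning hypothesis. This is a reason to keep it as a description.

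**Conclusion.** The point holds in a limited form. As written, the ECMO duration comparison does not distinguish successful weaning from bridging or death. For each bridged patient, and each patient who dies on ECMO, the raw count is shorter than the time without successful weaning. Between arms the result can be wrong-signed, blind or diluted. Which of these applies depends on bridging rate and timing, which the article does not give.

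Under the step 2 assumptions (weaning on day 8, an extra 5% to 20% bridged, bridging between day 4 and day 14), raw duration moves by −0.8 to +1.2 days, while days without weaning rise by 1.1 to 4.4. These figures show a mechanism and do not forecast the trial's result. The endpoint is exploratory and the confirmatory analysis of the Inotropic Score at 72 h is untouched, so the severity is low.

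**What to change.** In sections 2.7.2 and 2.12.2, define successful weaning as decannulation alive without LVAD or transplant. Analyse time to that event, to day 7 and to day 30, by cumulative incidence, with LVAD/transplant and death as competing events. Alternatively, keep the Mann–Whitney U test and score bridged and deceased patients as not weaned by day 30. Report raw ECMO days as descriptive only.

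Both events are needed. A repair aimed at death alone, such as days alive and free of ECMO, would still credit a patient bridged on day 6 with up to 30 − 6 = 24 good days.

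The cost is wording. Table 1 already collects ECMO duration and mortality to day 30, and section 2.7.2 assesses LVAD or transplant at day 30. The downside is that the result is given as cumulative incidence or ranks instead of mean days. If mortality on ECMO is high, the rank version will have many ties at the worst value and will behave much like a comparison of the proportions weaned.
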